# DOSE AJUSTMENT AND DISCONTINUATION OF ADMINISTRATION

## General Rules for Dose Adjustment

- Reasons for dose adjustments or delays in administration, measures taken, and results should be documented in the subject's medical record and electronic case report form (CRF).
- If concomitant symptoms were present at baseline, it was the investigator to decide whether the dose would be adjusted according to the level of change in the adverse effect. For example, a subject with a Grade 1 "weakness" status at baseline and a Grade 2 "weakness" status during the study treatment period may be considered a "weakness" condition. The dose should be adjusted for grade 1 toxicity.
- In the event that several adverse reactions of different grades or severity occur simultaneously, dose adjustments will be based on the highest grade observed.
- If a dose adjustment is required solely due to an abnormal laboratory hematology test, the dose will be adjusted based on the hematology test prior to the start of the treatment cycle.
- The current dose will be continued without dose adjustment or suspension of treatment when, in the evaluation of the investigator, the adverse reaction is unlikely to progress further to a serious or life-threatening event.
- If the toxicity is caused by another medication, no dosage adjustment of the other medication is necessary.
- Permanent discontinuation of one therapeutic agent prior to the onset of PD will not affect the continued use of other therapeutic agents.
- If one of the therapeutic medications is suspended due to an adverse reaction, but not all of the medications, the treatment is still counted as one treatment cycle.

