**Table 1. Dose Adjustment Provisions for Camrelizumab**

| **Adverse reaction** | **Severity** | **Dosage adjustment** |
| --- | --- | --- |
| Pneumonia | Grade 2 | Suspension of drug administration ^a^ |
|  | Grade 3 or 4 | Permanent discontinuation |
| Diarrhea/ Colitis | Grade 2 or 3 | Suspension of drug administration ^a^ |
|  | Grade 4 | Permanent discontinuation |
| Dermatitis | Grade 3 | Suspension of drug administration ^a^ |
|  | Grade 4 | Permanent discontinuation |
| AST, ALT, or Bilirubin  Increased | Grade 2 | Suspension of drug administration ^a^ |
|  | Grade 3 or 4 | Permanent discontinuation |
| Hypophysitis | Grade 2 | Suspension of drug administration ^b^ |
|  | Grade 3 or 4 | Permanent discontinuation |
| Adrenocortical Insufficiency | Grade 2 | Suspension of drug administration ^b^ |
|  | Grade 3 or 4 | Permanent withdrawal |
| Hyperthyroidism | Grade 3 or 4 | Permanent discontinuation |
| Type I Diabetes | Grade 3 | Suspension of drug administration ^b^ |
|  | Grade 4 | Permanent discontinuation |
| Renal Insufficiency | Grade 2 or 3 | Suspension of drug administration ^a^ |
|  | Grade 4 | Permanent discontinuation |
| Neurotoxicity | Grade 2 | Suspension of drug administration ^a^ |
|  | Grade 3 or 4 | Permanent discontinuation |
| Infusion Reaction | Grade 3-4 | Permanent discontinuation |
| Other AE | Other Grade 3 AE first occurrence | Suspension of drug administration ^a^ |
|  | Grade 3 AE occurred again | Permanent discontinuation |
|  | Fail to drop to grade 0-2/baseline level within 7 days or 14 days.  Grade 3 AE within 0-1/baseline levels | Permanent discontinuation |
|  | Grade 4 AE | Permanent discontinuation ^c^ |

a: Resume dosing after symptoms recover to grade 0-1 or baseline level.

b: Hypophysitis, adrenocortical insufficiency, and type I diabetes mellitus may resume dosing when they are adequately controlled and require only physiologic hormone replacement therapy.

c: For Level 4 abnormal laboratory results, the decision to discontinue the medication should be based on concomitant clinical signs/symptoms and in accordance with the investigator's clinical evaluation.

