**Table 3. Dose Adjustment Provisions for Apatinib**

| **NCI Toxicity Classification** | **Dose Adjustment for Hematologic Toxicity** |
| --- | --- |
| Grade 1, 2 Hematologic Toxicity | Maintain original dose level (appropriate symptomatic treatment) |
| Grade 3 Hematologic Toxicity | Firstly, suspend the drug and start symptomatic treatment, wait for the toxicity to recover to ≤ grade 2, then continue the treatment at the original dose |
| Grade 4 Hematologic Toxicity | Firstly, suspend the drug and start symptomatic treatment, wait for the toxicity to recover to ≤ grade 2, then continue the treatment at the original dose |
| **Dose Adjustment for Non-Hematologic Toxicity** | |
| Grade 1 Non-Hematological Toxicity | Maintain original dose level (appropriate symptomatic treatment) |
| Grade 2 Non-Hematological Toxicity | Symptomatic treatment, if the toxicity returns to ≤ grade 1 after two weeks, continue the drug; If the toxicity does not aggravated, suspend the drug and wait until the toxicity recovers to ≤ grade 1, continue to the original dose level. |
| Grade 3 Non-Hematological Toxicity | Suspend the drug and start symptomatic treatment, and continue treatment at the original dose when the toxicity recovers to ≤ grade 1; If grade 3 occurs again then discontinue related medication treatment. |
| Grade 4 Non-Hematological Toxicity | Suspend the drug and start symptomatic treatment, and continue treatment at the original dose when the toxicity recovers to ≤ grade 1. If it reccurs Grade 4 toxicity, terminate related drug therapy. (If life-threatening adverse events occur such as Grade4 renal damage, neurotoxicity, cardiotoxicity, hepatotoxicity, etc., terminate related drug therapy immediately) |
| Adverse reactions requiring special attention: In the event of hypertensive crisis, cerebral hemorrhage, ≥ Grade 2 pulmonary hemorrhage, ≥ Grade 3 other bleeding, arterial thrombosis, Grade 4 venous thrombosis, leukoencephalopathy syndrome, or gastrointestinal perforation, discontinue the administration of drugs associated with adverse effects and initiate prompt symptomatic treatment. | |

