**Non-hematologic toxicity**

Treatment should be delayed (up to 9 weeks) if any non-hematologic toxicity occurs until the value returns to baseline or below baseline (or Grade ≤ 1 if the subject has no toxicities at baseline). At the beginning of the subsequent cycles, the dose should be reduced based on the non-hematologic toxicity observed from the last cycle. Table 5 provides the dose modification recommendations for non-hematologic toxicity.

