**Table 5. Dose Modification or Treatment Discontinuation due to Non-Hematologic Toxicity**

| **Toxicity** | **Modified Carboplatin Dose (by % of Previous Dose)**^a^ | |
| --- | --- | --- |
| Diarrhea | Grade 3 or 4^b^ | 75% |
| Nausea/Vomiting^C^ | Grade 3 or 4 | 75% |
| Neurotoxicity | Grade 2 | 75% |
| Grade 3 or 4 | 50% or permanent discontinuation |  |
| AST, ALT, or Bilirubin  Increased | Grade 3 | 75% |
| Grade 4 | Discontinuation |  |
| Others | Grade 3 or 4 | 75% |

a The carboplatin dose can be modified by a specific percentage of the original AUC if deemed appropriate by the investigator. Previous dose: The calculated dose before dose administration of each cycle.
b Antidiarrheal agents are used for Grade 3-4 diarrhea or for any grade of diarrhea that requires hospitalization.
c Even when antiemetic therapy has been given.

Diarrhea should be treated with appropriate antidiarrheal agents. Nausea and/or vomiting should be treated with appropriate anti-emetics. If Grade 3 or 4 nausea/vomiting occurs, anti-emetics should be used and the dose should be reduced by 25% in the next cycle. The original dose should be resumed as soon as the subject is able to tolerate. If Grade 3 or 4 neurotoxicity occurs,chemotherapy should continue at 50% of the previous dose after improvement, or immediately be discontinued (based on the investigator's judgment).

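### Section 9.1 tells investigators to continue the current dose on their own judgment, with no exception for the Grade 2 camrelizumab suspensions in Table 1 or the Grade 2 pulmonary hemorrhage stop in Table 3

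*Protocol*

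**What the plan says.** Among the general rules in section 9.1 is this one: "The current dose will be continued without dose adjustment or suspension of treatment when, in the evaluation of the investigator, the adverse reaction is unlikely". The condition is completed by "the adverse reaction is unlikely to progress further to a serious or life-threatening event", and the sentence ends there. It mentions no grade, no table and no exception.

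The drug-specific rules follow.

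- **Camrelizumab (section 9.2, Table 1).** Actions are set by reaction and grade, for example "Pneumonia | Grade 2 | Suspension of drug administration". Under the footnotes, dosing resumes on recovery to Grade 0-1 or baseline. For hypophysitis, adrenocortical insufficiency and type I diabetes, it may resume once the condition is controlled on physiologic hormone replacement. Footnote c leaves one decision to clinical judgment: "For Level 4 abnormal laboratory results, the decision to discontinue the medication should be based on concomitant clinical signs/symptoms".
- **Apatinib (section 9.3, Table 3).** The last row begins "In the event of hypertensive crisis, cerebral hemorrhage, ≥ Grade 2 pulmonary hemorrhage, ≥ Grade 3 other bleeding" and, after listing further events, instructs the investigator to "discontinue the administration of drugs associated with adverse effects and initiate prompt symptomatic treatment".
- **Chemotherapy (section 9.4).** Table 5 has one Grade 2 row, "Neurotoxicity | Grade 2 | 75" (percent of the previous carboplatin dose). The accompanying text says "Treatment should be delayed (up to 9 weeks) if any non-hematologic toxicity occurs until the value returns to baseline or below baseline".

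Section 9.2 also refers to Annex VI for camrelizumab dose adjustment and toxicity management. The annex is not in the document at hand.

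**The concern.** The general rule and Table 1 give opposite instructions for the same event. Take a Grade 2 ALT rise, found only on laboratory testing, that the investigator expects to stay as it is. Section 9.1 says to carry on unchanged; Table 1 says to suspend camrelizumab until recovery.

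The primary endpoint is safety (section 2.1), and the dose rules are the main protection against immune-related and bleeding toxicity. If either instruction can be followed compliantly, protection depends on which one an investigator reads as controlling. Exposure after a Grade 2 event may then differ between investigators for reasons unrelated to the patient.

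**Working it through.** The protocol gives no figure to reproduce here. The check compares section 9.1 with each drug-specific provision that applies at Grade 2.

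**1. Scope of the 9.1 rule.** The wording is mandatory. The only condition is the investigator's expectation that the reaction will not become serious or life-threatening. That condition does limit the rule: section 13.6 treats hospitalization as serious, so an event expected to lead to admission falls outside it. A stable Grade 2 event managed as an outpatient falls inside it.

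**2. Table 1, row by row.** The table names 11 reactions, apart from the residual row for other events.

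- Suspension at Grade 2: pneumonia, diarrhea/colitis, AST/ALT/bilirubin increase, hypophysitis, adrenocortical insufficiency, renal insufficiency, neurotoxicity = 7.
- First action at Grade 3: dermatitis, hyperthyroidism, type I diabetes, infusion reaction = 4.
- Check: 7 + 4 = 11.

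In each of the seven rows, a Grade 2 event that meets the 9.1 condition is to be both continued and suspended. None of the seven carries wording that leaves the decision to the investigator. Footnote c does so only for Grade 4 laboratory results, which shows that Table 1 states discretion where it intends it.

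**3. Table 3.** The hemorrhage clause stops the responsible drug from Grade 2 upward for pulmonary bleeding. It offers no discretion, so it also conflicts with 9.1 as worded. The Grade 1-2 hematologic row keeps the dose unchanged and agrees with 9.1. The Grade 2 non-hematologic row is too garbled to rely on and is left out.

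**4. Table 2.** The Grade 1 and 2 infusion steps say what can be done, not what must be done. They do not contradict 9.1.

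**5. Section 9.4.** Its opening paragraph says carboplatin and etoposide doses may be adjusted and calls what follows a guideline. The text introducing Table 5 calls it recommendations, and footnote a of that table gives the investigator a choice over the basis of the reduction. The non-hematologic rule is a delay of the next cycle. The 9.1 rule bars adjustment and suspension but does not name delay, and the first bullet of 9.1 mentions adjustments and delays separately. These are softer inconsistencies and are not counted.

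**6. Precedence.** Nothing in sections 9.1 to 9.4 says whether the general rule or the tables control. Annex VI might settle this for camrelizumab, but it is not cited for apatinib.

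**Result:** seven Grade 2 rows in Table 1 and one Grade 2 stop in Table 3 are in direct conflict with 9.1.

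**The case against.** The strongest reply is that a specific rule displaces a general one. Section 9.1 is headed as general rules and 9.2 to 9.4 are drug-specific. Table 1's residual row starts at Grade 3, so unlisted Grade 1-2 events have no camrelizumab instruction, and the 9.1 rule fills that gap naturally. Read as an override, it would largely empty the seven Grade 2 rows.

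This is probably what the authors meant, but the text does not say it. Section 9.1 also changes how the tables apply elsewhere: its baseline-symptom bullet has a Grade 2 event over a Grade 1 baseline handled as Grade 1. A reader therefore has some reason to let the neighbouring bullet modify the tables too.

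A second reply is that few investigators would judge a Grade 2 pulmonary hemorrhage unlikely to worsen in this population, given that the background section itself raises bleeding under anti-vascular therapy. That is fair, and it makes the Table 3 conflict the less frequent one. It does not remove it.

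A reader might also infer that the conflict reaches all four study drugs through Table 5 and the chemotherapy delay rule. The documents do not support that: those provisions are a guideline, recommendations and a cycle delay, not firm adjustments or suspensions that 9.1 contradicts.

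**Conclusion.** The contradiction stands for camrelizumab at Grade 2 in 7 of 11 named reactions and, with less practical weight, for Grade 2 or higher pulmonary hemorrhage in Table 3. It should be fixed because it concerns a safety rule in a trial with safety as its primary endpoint.

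Its consequence is limited to subject protection and consistent exposure. A reader might infer that the primary safety data would be incomplete, but adverse events are graded and recorded whether or not the drug is continued. Nor can a number of affected subjects be given: the protocol states no expected incidence for these events among the 36 planned.

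The conclusion rests on two assumptions: that Annex VI does not settle precedence for camrelizumab, and that investigators will sometimes judge a listed Grade 2 event unlikely to become serious. If Annex VI does settle it, only the Table 3 conflict remains.

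**What to change.** Add to the section 9.1 bullet wording to this effect:

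> This rule applies only to events and grades for which sections 9.2 to 9.4 and their tables specify no action. Where they specify suspension, delay, dose reduction or discontinuation, those provisions govern, including any investigator discretion written into them (for example Table 1 footnote c; the opening and hematologic toxicity paragraphs of section 9.4; Table 5 footnote a; and the neurotoxicity text under Table 5).

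Phrasing it by what the sections specify, not what they require, brings the softer chemotherapy provisions under the same order of precedence while leaving their discretion intact. The bullet keeps its natural use for unlisted low-grade events.

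The cost is one clause in a protocol amendment and a memo to sites. The downside is small: investigators lose some latitude for the listed events.

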## Camrelizumab Dose Adjustment

Increasing or decreasing the dose of camrelizumab is not permitted, only suspension or discontinuation. The maximum permissible suspension interval for camrelizumab is 6 weeks (counted from the time of the last actual dose), otherwise treatment with camrelizumab is discontinued. If the investigator determines that the subject would benefit from continued dosing with suspension of camrelizumab for more than 6 weeks, it requires discussion with the drug sponsor.

Refer to Table 1 for camrelizumab dose adjustment provisions and Annex VI for camrelizumab dose adjustment and toxicity management guidelines. Refer to Table 2 for management of infusion reactions associated with camrelizumab.

In addition, subjects were evaluated PD per RECIST v1.1 criteria should be permanently discontinued treatment. Subjects were allowed to discontinue medication due to other medical, or surgical, or accidental events unrelated to the study treatment. Subjects should resume the study treatment within 2 weeks after the interruption of medication, unless the investigator has other resolutions. The reasons for discontinuing treatment must be recorded in the CRF table.

**Table 1. Dose Adjustment Provisions for Camrelizumab**

| **Adverse reaction** | **Severity** | **Dosage adjustment** |
| --- | --- | --- |
| Pneumonia | Grade 2 | Suspension of drug administration ^a^ |
|  | Grade 3 or 4 | Permanent discontinuation |
| Diarrhea/ Colitis | Grade 2 or 3 | Suspension of drug administration ^a^ |
|  | Grade 4 | Permanent discontinuation |
| Dermatitis | Grade 3 | Suspension of drug administration ^a^ |
|  | Grade 4 | Permanent discontinuation |
| AST, ALT, or Bilirubin  Increased | Grade 2 | Suspension of drug administration ^a^ |
|  | Grade 3 or 4 | Permanent discontinuation |
| Hypophysitis | Grade 2 | Suspension of drug administration ^b^ |
|  | Grade 3 or 4 | Permanent discontinuation |
| Adrenocortical Insufficiency | Grade 2 | Suspension of drug administration ^b^ |
|  | Grade 3 or 4 | Permanent withdrawal |
| Hyperthyroidism | Grade 3 or 4 | Permanent discontinuation |
| Type I Diabetes | Grade 3 | Suspension of drug administration ^b^ |
|  | Grade 4 | Permanent discontinuation |
| Renal Insufficiency | Grade 2 or 3 | Suspension of drug administration ^a^ |
|  | Grade 4 | Permanent discontinuation |
| Neurotoxicity | Grade 2 | Suspension of drug administration ^a^ |
|  | Grade 3 or 4 | Permanent discontinuation |
| Infusion Reaction | Grade 3-4 | Permanent discontinuation |
| Other AE | Other Grade 3 AE first occurrence | Suspension of drug administration ^a^ |
|  | Grade 3 AE occurred again | Permanent discontinuation |
|  | Fail to drop to grade 0-2/baseline level within 7 days or 14 days.  Grade 3 AE within 0-1/baseline levels | Permanent discontinuation |
|  | Grade 4 AE | Permanent discontinuation ^c^ |

a: Resume dosing after symptoms recover to grade 0-1 or baseline level.

b: Hypophysitis, adrenocortical insufficiency, and type I diabetes mellitus may resume dosing when they are adequately controlled and require only physiologic hormone replacement therapy.

c: For Level 4 abnormal laboratory results, the decision to discontinue the medication should be based on concomitant clinical signs/symptoms and in accordance with the investigator's clinical evaluation.

**Table 2. Treatment Recommendations for Camrelizumab Infusion Reactions**

| **CTCAE Classification** | **Dosage Adjustment** | **Toxicity Treatment** |
| --- | --- | --- |
| Any Grade |  | Manage according to clinical practice.  Monitor subjects for infusion-related reactions (e.g., fever or chills, flushing and/or itching, changes in heart rate and blood pressure, dyspnea, chest discomfort, rash, etc.) and allergic reactions (e.g., generalized urticaria, rash, angioedema, asthma, hypotension, tachycardia, etc.) |
| Grade 1 | The infusion rate can be adjusted downward by 50% or temporarily neutralized. Discontinue infusion until infusion reaction subsides. | For Grade 1 or 2:  Acetaminophen and/or antihistamines given at the investigator's discretion according to clinical practice.  Consider prophylactic medication before subsequent regimens according to local clinical practice. |
| Grade 2 | The infusion rate can be reduced by 50% or the infusion can be temporarily interrupted until the infusion response subsides.  Infusion rate adjustable to 50% of initial rate after that. |  |
| Grade 3/4 | Permanent discontinuation. | For Grade 3 or 4:  Manage severe infusion-related reactions according to local clinical practice (e.g., administer epinephrine, iphenhydramine, ranitidine and glucocorticoids) |

## Apatinib Dose Adjustment

The initial dosage of apatinib is 250mg once daily (250mg qd). If intolerable adverse effects occur, the dosage can be adjusted to 250mg every other day (250mg qod). If intolerance persists, discontinue the medication until symptoms reduce to Grade 1 or lower, then resume at 250mg qd. Permanent discontinuation is recommended if Grade 3 or higher adverse effects recur.

During treatment, suspension of administration is required for reasons of non-recovered drug toxicity, and the cumulative duration of dosing suspension should not exceed 2 weeks per dosing cycle to ensure that the subject receives the drug strength of the treatment. If the investigator determines that an adverse reaction is caused by apatinib, apatinib dosing may be suspended without affecting the use of other medications. Refer to Table 3 for apatinib dose adjustment.

**Table 3. Dose Adjustment Provisions for Apatinib**

| **NCI Toxicity Classification** | **Dose Adjustment for Hematologic Toxicity** |
| --- | --- |
| Grade 1, 2 Hematologic Toxicity | Maintain original dose level (appropriate symptomatic treatment) |
| Grade 3 Hematologic Toxicity | Firstly, suspend the drug and start symptomatic treatment, wait for the toxicity to recover to ≤ grade 2, then continue the treatment at the original dose |
| Grade 4 Hematologic Toxicity | Firstly, suspend the drug and start symptomatic treatment, wait for the toxicity to recover to ≤ grade 2, then continue the treatment at the original dose |
| **Dose Adjustment for Non-Hematologic Toxicity** | |
| Grade 1 Non-Hematological Toxicity | Maintain original dose level (appropriate symptomatic treatment) |
| Grade 2 Non-Hematological Toxicity | Symptomatic treatment, if the toxicity returns to ≤ grade 1 after two weeks, continue the drug; If the toxicity does not aggravated, suspend the drug and wait until the toxicity recovers to ≤ grade 1, continue to the original dose level. |
| Grade 3 Non-Hematological Toxicity | Suspend the drug and start symptomatic treatment, and continue treatment at the original dose when the toxicity recovers to ≤ grade 1; If grade 3 occurs again then discontinue related medication treatment. |
| Grade 4 Non-Hematological Toxicity | Suspend the drug and start symptomatic treatment, and continue treatment at the original dose when the toxicity recovers to ≤ grade 1. If it reccurs Grade 4 toxicity, terminate related drug therapy. (If life-threatening adverse events occur such as Grade4 renal damage, neurotoxicity, cardiotoxicity, hepatotoxicity, etc., terminate related drug therapy immediately) |
| Adverse reactions requiring special attention: In the event of hypertensive crisis, cerebral hemorrhage, ≥ Grade 2 pulmonary hemorrhage, ≥ Grade 3 other bleeding, arterial thrombosis, Grade 4 venous thrombosis, leukoencephalopathy syndrome, or gastrointestinal perforation, discontinue the administration of drugs associated with adverse effects and initiate prompt symptomatic treatment. | |

## Chemotherapy Dose Adjustment

The doses of carboplatin and etoposide may be adjusted based on the prescribing information and local treatment standards due to toxicities. The guideline for dose modifications is provided below. Once the dose is reduced, it cannot be increased back to 100% of the original dose. The treatment with carboplatin or etoposide should be discontinued if any Grade 3 or 4 hematologic or non-hematologic toxicity occurs after 2 dose reductions or a treatment delay of more than 9 weeks due to toxicity.

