**Hematologic toxicity**

The ANC should be ≥ 1500/μL and the platelet count should be ≥ 100,000/μL before starting each cycle. In order to provide sufficient time for recovery, the treatment can be delayed for up to 9 weeks. After 2 dose reductions or treatment delays exceeding 9 weeks due to toxicity, treatment with etoposide and/or carboplatin was discontinued unless the investigator believed that patients could benefit from continued treatment. Growth factor therapy may be provided as per the American Society of Clinical Oncology (ASCO) and NCCN guidelines (Smith et al. 2006; NCCN 2015). At the beginning of subsequent cycles after recovery, the dose should be modified based on the PLT and ANC nadirs of the last cycle (refer to Table 4). Subjects who require dose modification due to both ANC and PLT should receive a lower dose.

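### Section 9 gives conflicting rules on returning to full-dose chemotherapy, and restarts apatinib at the higher dose after the lower one was not tolerated

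*Protocol*

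**What the plan says.** **Chemotherapy after a reduction.** The opening paragraph of Section 9.4 covers carboplatin and etoposide: "Once the dose is reduced, it cannot be increased back to 100% of the original dose". The text after Table 5, on Grade 3 or 4 nausea and vomiting, says "anti-emetics should be used and the dose should be reduced by 25% in the next cycle" and then "The original dose should be resumed as soon as the subject is able to tolerate".

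**Apatinib.** Section 9.3 starts at 250 mg daily. It continues: "If intolerable adverse effects occur, the dosage can be adjusted to 250mg every other day (250mg qod". The next step is "If intolerance persists, discontinue the medication until symptoms reduce to Grade 1 or lower, then resume at 250mg qd". It then recommends a permanent stop if Grade 3 or higher effects come back. Table 3, to which Section 9.3 refers, has no alternate-day step. Its haematological Grade 3 and 4 rows and its non-haematological Grade 3 and 4 rows resume at the original dose, and its non-haematological Grade 2 row resumes at the original dose level when the drug has been suspended.

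**Stopping chemotherapy for haematological toxicity.** The opening of Section 9.4 stops carboplatin or etoposide if any Grade 3 or 4 "toxicity occurs after 2 dose reductions or a treatment delay of more than 9 weeks due to toxicity". It names haematological and non-haematological toxicity alike and gives no exception. The haematological part of Section 9.4 has a different trigger, which needs no further event: "After 2 dose reductions or treatment delays exceeding 9 weeks due to toxicity". In that situation it also leaves the investigator a way to go on: "treatment with etoposide and/or carboplatin was discontinued unless the investigator believed that patients could benefit from continued treatment".

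**The concern.** These rules apply to subjects who have just had severe or intolerable toxicity, in a trial whose primary endpoint is safety (Section 2.1) and which has a primary centre and a participating site (Abstract). An investigator has to act on one sentence or the other. Two sites following different sentences of Section 9.4 could give different doses to similar subjects, or one could stop where the other continues. The apatinib rule is a fault within a single paragraph: followed literally, it raises the dose in a subject who has already failed the reduced one. The protocol's own background (Section 1) notes that vascular involvement in this disease may raise the bleeding risk under anti-vascular treatment, so the direction of an apatinib dose step matters.

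Section 9.1 gives investigators some discretion and requires dose adjustments to be documented. It does not say which of the conflicting sentences governs.

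**Working it through.** The protocol states no figure on this point, so there is none to reproduce. The check sets the rules side by side and works out how far apart the resulting doses can be.

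**1. Chemotherapy after Grade 3 or 4 nausea or vomiting**

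Inputs: carboplatin AUC 5 per cycle; two induction cycles plus two to four combination cycles, so four to six in all (Section 8); a 25% cut in the next cycle (text after Table 5).

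Assumed worst case: the event is in cycle 1, the cut is in cycle 2, the original dose is tolerable from cycle 3, and there are no other reductions.

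- Six cycles, original dose resumed: 5 × (1 + 0.75 + 4) = 28.75.
- Six cycles, general bar applied, dose kept at 75%: 5 × (1 + 5 × 0.75) = 23.75.
- The bar excludes only 100%, so any total from 23.75 up to just under 28.75 complies with it. The excess is above 0 and at most 28.75 − 23.75 = 5.0; 28.75 / 23.75 = 1.21, or +21%.
- Illustration (assumption): re-escalation to 90% under the bar gives 5 × (1 + 0.75 + 4 × 0.9) = 26.75. The excess is then 2.0; 28.75 / 26.75 = 1.07.
- Four cycles: 5 × (1 + 0.75 + 2) = 18.75 against at least 5 × (1 + 3 × 0.75) = 16.25. The excess is at most 2.5; 18.75 / 16.25 = 1.15.
- If the cut falls in the last cycle, the difference is zero.

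**2. Apatinib after intolerance at the alternate-day dose**

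- Daily: 21 × 250 = 5,250 mg per 21 days.
- Alternate days: 10 or 11 doses × 250 = 2,500 or 2,750 mg per 21 days.
- Ratio: 5,250 / 2,750 = 1.91 to 5,250 / 2,500 = 2.10.

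The sequence is: daily dose not tolerated, alternate-day dose not tolerated, interruption, daily dose again. Table 3 does not correct this. It has no alternate-day step, and if original dose there means the starting dose, it also sends the subject back to 250 mg daily.

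**3. Haematological stopping rule (lesser)**

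- Two reductions, no further Grade 3 or 4 event: the opening of Section 9.4 continues treatment; the haematological part stops it unless the investigator sees benefit.
- Two reductions, then a further Grade 3 or 4 haematological event: the opening stops with no exception; the haematological part leaves room for the investigator to continue.
- Delay of more than nine weeks: the opening can be read in two ways. Either the delay alone stops treatment with no exception, or a Grade 3 or 4 event after such a delay is needed. Both differ from the haematological part, where the delay alone stops treatment subject to the investigator's view.

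If the two reductions fall in cycles 2 and 3 and no further event occurs, at most cycles 4 to 6 (three of six), or cycle 4 (one of four), are affected.

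**The case against.** The strongest case for the text as it stands is this. The nausea and vomiting sentence may be meant as a specific exception to a general rule, and Section 9.4 calls its content a guideline and lets doses follow the prescribing information and local standards. The apatinib restart is at the protocol's own starting dose, only after recovery to Grade 1 or lower, with a permanent stop recommended if Grade 3 or higher effects recur. It agrees with Table 3's return to the original dose, so it may be policy, or it may be a slip for alternate days. The haematological paragraph can be taken as the specific rule, and its investigator exception often permits the same continuation as the opening paragraph.

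Part of this stands. The haematological point is small and ranks below the other two. Calling the apatinib restart unsafe would be a clinical judgement, and the protocol holds no evidence on harm. The remainder does not stand. No sentence marks the nausea rule as an exception, and the general rule says a return to full dose cannot happen. A slip is still the operative instruction until it is corrected. The opening of Section 9.4 names haematological toxicity expressly, so the later paragraph does not simply displace it.

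A reader might go further and infer that Section 9.3 and Table 3 also conflict on recurrence stops and recovery thresholds. The text does not establish that. Section 9.3 is triggered by intolerability and Table 3 by grade, so they can partly be read as layered rules, and the absence of a haematological recurrence stop in Table 3 may be deliberate. Nor is there a matching clash for non-haematological toxicity, where Section 9.4 contains no general investigator exception.

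**Conclusion.** The point holds. Two faults are clear on the current text: the conflict over returning to full-dose chemotherapy after nausea or vomiting, and the apatinib restart at about twice (1.9 to 2.1 times) the dose just not tolerated. The haematological stopping rules also differ in trigger and in investigator exception, which is a lesser inconsistency. These should be fixed.

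The carboplatin figures are upper bounds: at most AUC 5.0 (+21%) over six cycles and AUC 2.5 (+15%) over four, resting on an event in cycle 1, no other reductions, and a dose held at 75% under the general bar. The true gap could be close to zero. A reader might take +21% as the expected difference, or infer a bias of known size in the toxicity rates. The protocol supports neither. It does not say how often these situations arise, and the trial is single-arm with a mainly descriptive safety analysis (Section 14.4). The effect is on subjects' dosing and on consistency between sites.

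**What to change.** 1. **Section 9.4, re-escalation.** Either name Grade 3 or 4 nausea and vomiting as an exception to the bar in the opening paragraph, or delete the resumption sentence after Table 5.
2. **Section 9.3 and Table 3, apatinib.** After intolerance at 250 mg on alternate days, restart at no more than that dose once symptoms are Grade 1 or lower, or discontinue permanently. State in Table 3 that original dose means the dose level in use when the event occurred, so that no subject who failed the alternate-day dose returns to daily dosing. Both changes are needed: correcting Section 9.3 alone would leave Table 3 open to the old reading.
3. **Section 9.4, haematological stopping.** Use one trigger in the opening paragraph and the haematological part, give the nine-week clause a single reading, and state the investigator exception once.

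No new recurrence stops are proposed for Table 3; those would be a clinical change beyond resolving these inconsistencies. The cost is a protocol wording amendment, which Section 16 requires to be resubmitted to the Ethics Committee. Sample size, visits and analysis do not change.
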